**Pre-existing medical conditions**

Any pre-existing symptoms/signs in subjects during the study screening period should only be recorded and reported as AEs upon entering the study if there is an increase in severity, frequency, or nature (excluding worsening of the studied disease condition). The record should reflect changes relative to the previous condition, such as "increased frequency of headaches."

**Disease progression**

Disease progression is defined as the worsening of the subject's condition due to the primary tumor targeted by the study drug; the emergence of new lesions relative to the primary tumor or the progression of existing lesions is considered disease progression. Expected disease progression is not reported as an AE. Death, life-threatening conditions, hospitalization or prolonged hospitalization, persistent or significant disability/incapacity, congenital anomalies/birth defects, or other important medical events resulting from symptoms and signs of expected disease progression are not subject to expedited reporting as SAEs.

- 1. **Expedited Reporting of SAEs and Pregnancy**

**Reporting of SAEs:**

The reporting period for SAEs is from the signing of the informed consent to 30 days after surgery (inclusive). In the event of an SAE, whether it is an initial report or a follow-up report, the investigator must promptly complete the Serious Adverse Event Report Form, sign and date it, and report it to the sponsor within 24 hours of becoming aware of the event. Meanwhile, SAEs occurring after using Henlius products shall be reported to Henlius: ([contact]) within 24 hours after awareness, and the SAE occurring after using SciClone products shall be reported to SciClone ([contact]) within 24 hours after awareness.

If a SAE occurring outside the aforementioned period is determined to be related to the study drug, it should also be reported.

**Pregnancy:**

As similar drugs have been associated with embryotoxic safety risks, all subjects of childbearing potential participating in the clinical study must take effective contraceptive measures.

If a female subject becomes pregnant during the clinical study while exposed to the study drug, the subject will be withdrawn from the study. The sponsor, Henlius, and SciClone's pharmacovigilance departments must be notified within 24 hours of the investigator's awareness of the pregnancy. If the partner of a male subject exposed to the study drug becomes pregnant during the clinical study, the subject may continue participation in the study. The pregnancy must be reported to the sponsor, Henlius, and SciClone's pharmacovigilance departments within 24 hours of the investigator's awareness of the pregnancy.

The investigator shall continuously monitor subjects who become pregnant and follow up on the pregnancy outcomes until 8 weeks after maternal delivery, and report the results to the sponsor, Henlius, and SciClone.

If the pregnancy outcome is stillbirth, spontaneous abortion, fetal malformation (any congenital anomaly/birth defect), or medically indicated termination of pregnancy, it shall be considered an SAE and must be reported following the procedures and within the timelines for SAEs.

If a subject experiences an SAE during pregnancy, it shall be reported following the SAE reporting procedures.

- 1. **Immune-Related Adverse Events**

Given that the mechanism of action of Serplulimab involves T-cell activation and proliferation, irAEs may be observed during this study. Subjects should be monitored for signs and symptoms of irAEs. In the absence of a clearly identified alternative etiology (e.g., infection), signs or symptoms of illness occurring in the subject during the study should be considered related to the immune system.

For dose adjustments of Serplulimab and management principles for AEs, please refer to Section 8 of the protocol.

1. **Statistical Approach**
   1. **Statistical Analysis Data Set**

Full Analysis Set (FAS): Based on the principle of ITT, including patients who have received Serplulimab and with one efficacy evaluation. For case data where the full treatment course is not observed, the last observation carried forward (LOCF) will be used to carry forward the last observation data to study final result. ITT is the primary study population for this study.

Per-protocol Set (PPS): Including all patients that comply with the study protocol, have good compliance, do not take prohibited medications during the study, and complete the required content in the case report forms. No imputation will be made for missing data. Statistical analyses of the drug's efficacy will be performed based on both the FAS and PPS.

Safety Analysis Set: Including all enrolled patients who have received at least one complete cycle of neoadjuvant immunotherapy plus chemotherapy and have safety records after using Serplulimab. This data set is used for safety analysis.

- 1. **Statistical Analysis Plan**

The results of this study will be primarily analyzed using statistical descriptive methods. For measurement data, the mean, standard deviation, median, max, and min values will be listed. For enumeration data and ranked data, the frequency (constituent ratio), rate, and CIs will be listed.

All statistical analyses will be programmed and calculated using SAS 9.2 Statistical Analysis Software. All statistical tests will be performed using two-sided tests, where P < 0.05 will be considered statistically significant for the tested differences, and CIs will be presented as 95% CIs.

- 1. **Efficacy Analysis**

The primary efficacy endpoint is the pCR rate. The ORR and its 95% CI will be calculated by the best overall response (BOR).

The Kaplan-Meier method will be used to plot the DFS curve and estimate the median DFS with its 95% CI, as well as the OS curve and its 95% CI.

Statistical analysis will be performed using SAS 9.4 software, where P < 0.05 will be considered statistically significant for the tested difference.

- 1. **Drug Safety Evaluation**

The AEs and adverse reactions that occurred in this study will be primarily described by descriptive statistical analysis, with a listing provided (adverse reactions are defined as “AEs with a ‘definitely related/probably related/possibly related’ relationship to the study drug”). The laboratory test results describe the conditions where values are normal before treatment but become abnormal afterward, along with the relationship with the study drug in case of abnormal changes. Chi-square test will be performed for the incidence of related adverse reactions between different stratified groups.

1. **Quality Control and Quality Assurance**

The study personnel must be physicians trained in clinical trials and work under the supervision of senior professionals.

The clinical wards are inspected before the study, which must meet standardized requirements to ensure the availability of complete resuscitation equipment.

It is recommended that medications be administered to patients by professional healthcare personnel who have a thorough understanding of the drug regimen to ensure patient compliance.

The investigator must accurately complete the case report form.

The investigator shall adhere to standard operating procedures, oversee the conduct of the clinical study, verify that all data are recorded and reported accurately and completely, and all case report forms are completed correctly and are consistent with source documents, and guarantee that the study is conducted in compliance with the clinical study protocol.

In the event of an SAE, it must be promptly reported to the Ethics Committee, and the study may be temporarily suspended if necessary.

1. **Ethical, Regulatory, and Administrative Principles**
   1. **Ethical Principles**

This study will be conducted in accordance with the principles established by the 18th World Medical Association (Helsinki, 1964) and all subsequent amendments.

- 1. **Laws and Regulations**

This study will be conducted in compliance with all applicable laws and regulations.

- 1. **Data Protection**

Patient personal data and investigator personal data that may be included in the EDC system shall be processed in accordance with all applicable local laws and regulations.

When personal data related to investigators and/or patients are archived or processed, the study director or principal investigator shall take all appropriate measures to protect and prevent unauthorized third parties from accessing such data.

- 1. **Confidentiality Agreement**

All materials, information (oral or written), and unpublished documents provided to the investigator (or any actions performed by the sponsor on behalf of the investigator), including this protocol and CRF, shall not be disclosed by the investigator or study personnel at each site to unauthorized personnel without the prior formal written consent of the leading site.

Except for information that may be disclosed as permitted by regulations, the investigator shall maintain confidentiality regarding all information received, obtained, or derived during this study and shall take all necessary steps to ensure no unauthorized disclosure occurs.

- 1. **Record Safekeeping**

The investigator shall arrange for the safekeeping of study documents until the completion of the study. In addition, for the safekeeping of patient records, the investigator must comply with specific local regulations/guidelines.

Unless otherwise specified in the investigator agreement, it is recommended that the investigator retains study documents for at least five years after the completion or termination of the study, in accordance with other standards and/or local regulations.

- 1. **Early Suspension of Study**

The sponsor may decide to suspend this study at any time and for any reason; the decision to suspend the study will be communicated in writing to the investigators at each site.

Similarly, if the investigator at each site decide to withdraw from the study, he/she must notify the sponsor in writing.

Where applicable, the Institutional Review Board (IRB) and health regulatory authorities should be notified in accordance with local regulations.

- 1. **Sponsor's Audits and Regulatory Authority's Inspections**

The investigators at each site agrees to allow the sponsor's auditors/inspectors from regulatory authorities have direct access to patient study records for review purposes, and acknowledge that these individuals are bound by professional confidentiality principles, thus they will not disclose any personally identifiable or personal medical information of the patients.

The investigator at each site will make every effort to facilitate audits and inspections, ensuring that auditors/inspectors have access to all necessary equipment, data, and documents.

During these inspections, the confidentiality of validation data and the protection of patients shall be respected.

The investigators at each site should promptly communicate the results and information provided by regulatory authorities following inspections to the sponsor.

The investigators at each site shall take appropriate measures as required by the sponsor to implement corrective actions for all issues identified during audits or inspections.

- 1. **Protocol Amendments**

Any amendments to the protocol will be documented in a written revision, and signed by the investigators at each site. The signed revision will be appended to this protocol.

Amendments to this protocol may be submitted in accordance with local regulations.

- 1. **Ownership and Use of Study Data and Results**

The sponsor has full access to the final data to enable appropriate academic analysis and reporting of the study results.

- 1. **Publication**

Any subsequent disclosure or publication by study participants (including substudies) must be approved by the sponsor and cite this study and the initial publication.

The sponsor may request that the sponsor's name and/or the name(s) of one or more employees of the sponsor be included or excluded from this publication.

The sponsor may delay publication or communication for a limited period to protect the confidentiality or proprietary nature of any information contained therein.

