| Administration Method of the Study Drugs | Neoadjuvant therapy phase:  Serplulimab: 300 mg, i.v., D1, Q3W;  Thymalfasin: 4.8 mg, subcutaneous injection, twice a week. On Day 1 and Day 4 of each week during Weeks 1–9 or until surgery;  Oxaliplatin: 130 mg/m2, i.v., D1, Q3W;  Tegafur: oral administration: body surface area < 1.25 m^2^, 40 mg each time; body surface area ≥ 1.25 to < 1.5 m^2^, 50 mg each time; body surface area ≥ 1.5 m^2^, 60 mg each time, twice daily for each treatment cycle at D1-D14  After 3 courses of treatment before surgery, radical gastrectomy will be conducted based on evaluation by the investigator within 2–6 weeks after completion of chemotherapy + immunotherapy.  Adjuvant therapy phase: The postoperative treatment of patients will be jointly decided by clinical physicians and patients according to the actual conditions of clinical diagnosis and treatment. |
| **Evaluation Criteria** | Efficacy evaluation:  Evaluation per RECIST v1.1 criteria:   - Pathologic complete response (pCR) rate, defined as the proportion of subjects with no residual viable tumor cells under microscopic examination and negative lymph nodes among the total subjects; - Major pathologic response (MPR) rate, defined as the proportion of subjects with ≤10% viable tumor cells in the resected specimen among the total subjects; - Tumor regression grade (TRG) - Objective response rate (ORR), defined as the proportion of subjects achieving complete response (CR) and partial response (PR) among the total subjects; - Clinical downstaging rate: ypT0 ratio, ypN0 ratio, and preoperative imaging clinical stage will be counted, respectively, to compare with baseline imaging clinical stage downstaging ratio. - Disease-free survival (DFS), defined as the time from surgery to the first radiological disease recurrence or death (whichever occurs first); - Overall survival (OS), defined as the time from enrollment to death of the subject due to any cause;   Safety evaluation:   - Drug-related safety (per CTCAE 5.0): incidence, relationship to study drug and severity of TRAEs, TRAEs ≥ Grade 3, irAEs, etc. - Surgery-related safety (according to Dindo-Demartines-Clavien classification). |

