Through reviewing its mechanism of action, thymalfasin is an immunological peptide with 28 amino acids, which has potential therapeutic effects on patients with various tumors (such as liver cancer, lung cancer, and lymphoma) and diseases (including infectious diseases and chronic hepatitis B), as well as immune improvement effects (*e.g.*, enhancing the response to vaccine) on patients with immunologic inadequacy. It mainly acts on Toll-like receptor 2 (TRL2) and TRL9 on dendritic cells (DCs), and stimulates intracellular signaling pathways including the NF-κB and p38 MAPK pathways, thus increasing the activity of natural killer (NK) cells. Moreover, it promotes the conversion of helper T (Th) cells to Th1 subset, increases the expression of Th1-type cytokines like IL-2 and IFN-γ, elevates the level of cytotoxic T lymphocytes (CTLs), and facilitates DC activation. Tumor cells can be killed through the combined action of NK cells, cluster of differentiation 4 (CD4)^+^ Th1 cells and CTLs. Meanwhile, activated DCs can also generate anti-tumor responses and perform efficient antigen presentation.

Based on the above background and basis, we designed this study to investigate the efficacy and safety of Serplulimab in combination with thymalfasin and SOX regimen for neoadjuvant therapy of locally advanced gastric cancer, and look forward to exploring safer and more effective neoadjuvant regimens for such patients to further benefit patients with gastric cancer.

1. **Objectives and Endpoints**
   1. **Objectives**
2. Primary objective: To investigate the efficacy and safety of Serplulimab in combination with thymalfasin and SOX regimen for neoadjuvant therapy of locally advanced gastric cancer.
3. Secondary objective: To investigate the effect of neoadjuvant therapy with Serplulimab in combination with thymalfasin and SOX regimen on tumor immune micro-environment in locally advanced gastric cancer.
   1. **Endpoints**
      1. **Primary Endpoint**

- Pathological Complete Response (pCR): For patients with surgically resectable gastric cancer after neoadjuvant therapy, the proportion of patients with no residual tumor cells in the primary site to the total enrolled patients.
  - 1. **Secondary Endpoints**
- Major Pathological Response (MPR): For patients with surgically resectable gastric cancer after neoadjuvant therapy, the proportion of patients with less than 10% residual tumor cells in the primary site to the total enrolled patients.

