- Tumor Regression Grade (TRG): It is intended to grade the pathological response of tumor after neoadjuvant therapy and generally divide the grade mainly according to the proportion of fibrosis and residual tumor in the tumor. In this study, Becker criteria are used to grade TGR as follows: TRG1a (no residual tumor), equivalent to pCR; TRG1b (< 10% residual tumor); TRG2 (10% to 50% residual tumor); and TRG3 (> 50% residual tumor). For patients with surgically resectable gastric cancer after neoadjuvant therapy, the proportion of patients with less than 10% residual tumor cells in the primary site to the total enrolled patients (TRG1a & TRG1b).
- Clinical downstaging rate (T and/or N downstaging): ypT0 ratio, ypN0 ratio, and preoperative imaging clinical stage will be counted, respectively, to compare with baseline imaging clinical stage downstaging ratio.
- Objective response rate (ORR): It refers to the proportion of patients whose tumor shrinks to a certain extent and remains for a certain period of time, including CR (Complete Response) and PR (Partial Response) cases. Objective tumor response will be assessed using Response Evaluation Criteria in Solid Tumors (RECIST 1.1 criteria). Patients must have measurable tumor lesions at baseline. Response evaluation criteria are divided into Complete Response (CR), Partial Response (PR), Stable Disease (SD) and Progressive Disease (PD) according to RECIST 1.1 criteria.
- Disease control rate (DCR): It refers to the percentage of confirmed complete response (CR), partial response (PR) and stable disease (SD) cases among evaluable efficacy patients.

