- Disease-free Survival (DFS): Disease-free survival refers to the time from the start of randomization to disease recurrence or death due to disease progression. DFS will be defined as the last date the patient is last confirmed to be disease-free survival if the patient does not experience disease progression during the study. Patients who discontinue the trial for reasons other than disease progression (no subsequent imaging) and patients who receive treatment after the trial will be censored at the time of discontinuation or the time of initiation treatment after the trial. When patients are not censored at the time of discontinuation from the trial or the time of initiation treatment after the trial, pre-planned sensitivity statistical analyses will further confirm DFS based only on the time of event of radiologically confirmed progression. New onset of other tumors are not considered as disease progression events and are not censored. If an imaging examination and evaluation show disease progression, the date of disease progression will not be the imaging examination date when disease progression is first shown, but the imaging examination date when disease progression is clearly confirmed. If disease progression is diagnosed by other clinical modalities, the date of diagnosis will be used as the date of disease progression.
- Overall Survival (OS): Overall survival refers to the date from enrollment to death due to any cause. For patients who are alive at last follow-up, their OS will be censored based on the time of last follow-up. For patients who are lost to follow-up, their OS will be censored based on the last confirmed survival time before loss to follow-up. The OS of data censor is defined as the time from enrollment to censoring.
- R0 resection rate: R0 resection rate refers to the proportion of patients who complete R0 resection in the total number of enrolled patients with surgically resectable gastric cancer through 3 cycles (21 days per cycle) of treatment with Serplulimab in combination with SOX regimen and 9 weeks of thymalfasin. Of these, R0 resection refers to negative microscopic margins.

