- Safety of neoadjuvant immunization + chemotherapy + thymalfasin: Observe any adverse events occurred in all patients during the clinical study, including abnormalities in laboratory tests of abnormal clinical symptoms and vital signs, record their clinical manifestations, severity, occurrence time, duration, treatment methods and prognosis, and determine their correlation with the test drug. Drug safety will be evaluated by NCI-CTCAE version 5.0 criteria. Meanwhile, the incidence of Grade 3–4 adverse events will be recorded from the start of neoadjuvant therapy to 30 days after surgery; the proportion of neoadjuvant therapy-related AEs causing surgical delay more than 30 days or inoperable beyond the original plan;
  - 1. **Exploratory endpoints**

Biopsy tissue specimens before neoadjuvant therapy and paraffin-embedded pathological tissue specimens after surgery will be collected from cases meeting the inclusion and exclusion criteria, and the expressions of CD68, CD86, CD163, CD4+T cells, and CD8+T cells will be detected.

1. **Study Design**

This is a prospective, open-label, single-arm phase II clinical study to assess the efficacy and safety of Serplulimab in combination with thymalfasin and SOX regimen for neoadjuvant therapy of locally advanced gastric cancer. It is planned to enroll 30 patients with HER2-negative gastric or gastroesophageal junction adenocarcinoma confirmed by histopathology and/or cytology who were clinically staged as stage III resectable G/GEJ carcinoma (Siewert type III and Siewert type II not requiring combined thoracotomy) as assessed by endoscopic ultrasonography, CT/MRI and other imaging. Endoscopically, gastric tumor tissues will be collected from patients for immunofluorescence detection while clamping gastric tumors for pathological examination.

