8. The surgery should be performed within Weeks 2–6 after the completion of the last chemotherapy + immunotherapy. The R0 resection rate of surgery in the overall patient population should be assessed. Tumor tissue from surgically resected specimens should be collected for immunofluorescence assay. Postoperative pathological specimens should be evaluated for pCR, MPR, and TRG (marking the conclusion of the study-related treatment). Blood tests such as hematology, blood biochemistry, urinalysis, and coagulation function should be completed within 3–7 days after surgery.

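### The full analysis set labelled ITT requires an efficacy evaluation and uses LOCF, which contradicts a pCR rate defined over all enrolled patients and raises it whenever an unevaluated patient is dropped

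*Protocol*

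**What the plan says.** **Primary endpoint.** Protocol Section 2.2 defines pCR as "the proportion of patients with no residual tumor cells in the primary site to the total enrolled patients". The synopsis, under Evaluation Criteria, has it "defined as the proportion of subjects with no residual viable tumor cells under microscopic examination and negative lymph nodes among the total subjects". (The two also differ on lymph nodes, which is a separate matter.)

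**Analysis set.** Section 12.1 bases the full analysis set (FAS) on the ITT principle, "including patients who have received Serplulimab and with one efficacy evaluation". For courses not observed to the end, "the last observation carried forward (LOCF) will be used to carry forward the last observation data to study final result". It then names ITT as the primary population without defining any ITT set other than this FAS. Efficacy is to be analysed on the FAS and the per-protocol set (PPS).

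**Timing.** Under Section 6.2, pCR, MPR and TRG are read on the postoperative specimen. Under Sections 6.2 and 10, the efficacy evaluations before surgery are imaging: one in the week before Cycle 3 and one in the week after Cycle 3.

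**Secondary denominators.** The synopsis puts ORR over total subjects, while Section 2.2 puts DCR "among evaluable efficacy patients". Section 2.2 counts R0 resections "in the total number of enrolled patients with surgically resectable gastric cancer through 3 cycles", while Section 6.2 states: "The R0 resection rate of surgery in the overall patient population should be assessed".

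**The concern.** A single-arm trial rests on one proportion, so its denominator has to be fixed before results are seen. Here the endpoint definition and the analysis-set definition give different denominators, and no listed set matches the one in Section 2.2. The protocol does not say that a patient without surgery or pathology counts as a non-responder.

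Two things are at stake. First, the condition of one efficacy evaluation can remove only patients without pCR, so it can move the rate only upward. Second, LOCF presumes repeated measurement of the same quantity, whereas pCR has no earlier value to carry forward. With 30 patients, one patient is worth 3.3 points, so a choice made after the data are known could visibly change the reported result.

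**Working it through.** **Inputs**
- N = 30. Section 3: "It is planned to enroll 30 patients with HER2-negative gastric or gastroesophageal junction adenocarcinoma".
- The number of patients outside the FAS, d, is not given. Assumption: 0 to 6 of 30.
- The number of pCRs, x, is unknown. For illustration, 6 and 9 are used (20.0% and 30.0% of 30).
- The protocol states no null rate, target rate or power, so there is no figure of its own to reproduce.

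**Step 1: direction.** pCR needs a surgical specimen. A patient with no efficacy evaluation has no specimen and is therefore a non-pCR. Removing d such patients leaves x unchanged:
- rate over all enrolled = x/30
- rate in the FAS = x/(30-d)
- ratio = 30/(30-d): 30/29 = 1.03, 30/27 = 1.11, 30/24 = 1.25

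**Step 2: size**, with exact (Clopper-Pearson) 95% intervals:

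| d | 6 pCRs | Gain (points) | 9 pCRs | Gain (points) |
|---|---|---|---|---|
| 0 | 6/30 = 20.0% (7.7 to 38.6) | 0 | 9/30 = 30.0% (14.7 to 49.4) | 0 |
| 1 | 6/29 = 20.7% (8.0 to 39.7) | 0.7 | 9/29 = 31.0% (15.3 to 50.8) | 1.0 |
| 3 | 6/27 = 22.2% (8.6 to 42.3) | 2.2 | 9/27 = 33.3% (16.5 to 54.0) | 3.3 |
| 6 | 6/24 = 25.0% (9.8 to 46.7) | 5.0 | 9/24 = 37.5% (18.8 to 59.4) | 7.5 |

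**Step 3: who is lost.** Cycles last 21 days, so Cycle 3 starts on day 1 + 2 × 21 = 43 and the first scan falls on about days 36 to 42. Section 10 uses the term efficacy evaluation for imaging. On that reading the FAS loses mainly patients who die, withdraw or are lost before that scan, plus any enrolled but never given serplulimab. If the term meant pathology, every unoperated patient would be lost and d would be larger. Section 12.1 does not define it.

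**Step 4: LOCF.** For an unoperated patient the last observation is a scan. Carrying forward a result other than CR as non-pCR adds nothing. Carrying forward an imaging CR as pCR would add 1/30 = 3.3 points per patient (6/30 = 20.0% becomes 7/30 = 23.3%). The protocol has no rule for converting one into the other.

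**The case against.** The strongest case against is that little may be lost in practice. Progression seen on a scan is itself an evaluation. A patient who completes treatment but is not operated on has two scheduled scans. For patients stopping because of intolerable toxicity, Section 10 asks for an evaluation at discontinuation if none was done in the previous 4 weeks. Eligibility requires ECOG 0 to 1, expected survival of at least 3 months and judged resectability. This stands as a limit on size. It does not cover early death, withdrawal of consent or loss to follow-up, and it does not reconcile the two denominators.

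A reader might infer more than the text supports:
- **That the primary result is inflated regardless.** It is not; with d = 0 there is no bias.
- **That patients with progression, toxicity or no surgery generally vanish.** If imaging counts, most of them stay in.
- **That LOCF inflates pCR.** It would do so only if an imaging CR were relabelled as pCR, which the protocol nowhere instructs.
- **That exclusions could turn the trial positive against the background pCR rate of about 20% in Section 1.** The protocol sets no null rate and its analysis is mainly descriptive, so crossing 20% triggers nothing. In the table the lower limit never exceeds 18.8%.
- **That Section 2.2 divides R0 by operated patients.** Inclusion criterion 3 requires every enrolled patient to be judged suitable for R0 resection, so the wording can also mean all enrolled. It is ambiguous, not clearly wrong.

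The pCR definition in Section 2.2 also opens with a qualifier about patients resectable after neoadjuvant therapy, so it is less clean than its closing words suggest. Finally, a statistical analysis plan might handle missing pathology in detail. But the protocol does not leave this open: it states a rule that conflicts with its own endpoint.

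**Conclusion.** The contradiction stands. The primary endpoint is defined over all enrolled patients, but the set designated for its analysis drops those not given serplulimab or without an efficacy evaluation. The effect is conditional: the rate is multiplied by 30/(30-d) for d dropped patients who have no pCR. That is 0 to 5.0 points at 6 pCRs and 0 to 7.5 points at 9 pCRs for d from 0 to 6. Both the range of d and the pCR counts are assumptions. If imaging counts as an evaluation, as Section 10 suggests, d is probably confined to early losses and undosed patients.

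LOCF is the wrong tool for a pathological endpoint read once, but no direction of bias can be assigned to it. The R0 wording and the differing ORR and DCR denominators are inconsistencies to reconcile; no size of bias is claimed for them.

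**What to change.** - **Section 12.1, primary set:** define the primary efficacy set as all enrolled patients, with no efficacy-evaluation condition. If all patients who received any study drug is preferred, change Section 2.2 and the synopsis to match.
- **Section 12.1, missing data:** delete LOCF for pCR and the other pathological endpoints. State that patients with no surgery or no evaluable specimen count as non-pCR and non-MPR.
- **Supportive analyses:** show evaluable-only, resected-only and PPS rates beside the primary rate, labelled as such.
- **Secondary denominators:** reconcile R0 between Sections 2.2 and 6.2, and ORR and DCR between the synopsis and Section 2.2.

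The cost is a wording amendment and no new data. The downside is somewhat lower reported rates if any patients are lost before evaluation.
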